## **PHASE III CLINICAL TRIAL FOR AMERICAN TEGUMENTARY LEISHMANIASIS. EQUIVALENCE BETWEEN THE STANDARD AND ALTERNATIVE SCHEME WITH MEGLUMINE ANTIMONIATE.**

### **Subprojects**

- A. Controlled, randomized, double-blind, and phase III clinical trial to verify the equivalence of effectiveness and compare the safety between standard and alternative dose regimens of meglumine antimoniate in the treatment of cutaneous leishmaniasis.
- B. Development and application of methodologies for analysis of antimony speciation in patients with leishmaniasis treated with meglumine antimoniate.
- C. Comparison of the anti-*Leishmania* immune response in patients with American cutaneous leishmaniasis treated with standard or alternative dose of meglumine antimoniate.
- D. Comparison of *in vitro* cellular immune response to reference and parasite antigens isolated from the respective American tegumentary leishmaniasis patients who evolved to cure or reactivate the lesions after antimonial therapy
- E. Evaluation of genetic variability and *in vitro* antimonial sensitivity of *Leishmania* (V.) *braziliensis* samples isolated from patients before and after treatment with standard or alternative regimen of meglumine antimoniate.
- F. Blind study to evaluate the effectiveness and safety of intralesional meglumine antimoniate in patients with cutaneous leishmaniasis and contraindication to systemic therapy.
- G. Blind study to evaluate the effectiveness and safety of intralesional meglumine antimoniate in the treatment of patients with cutaneous leishmaniasis excluded from subproject A (systemic treatment with meglumine antimoniate).
- H. Phase III clinical trial for mucocutaneous or mucosal leishmaniasis. Comparison between the standard and alternative scheme with meglumine antimoniate.
- I. Blind study to evaluate the effectiveness and safety of intermittent low dose meglumine antimoniate in the treatment of patients with mucosal leishmaniasis excluded from the H subproject (standard or continuous low dose regimen).

J. Evaluation of patients' adherence in the Phase III clinical trial with standard and alternative scheme with meglumine antimoniate in the treatment of American cutaneous leishmaniasis.

K. Clinical-molecular study on mucosal leishmaniasis: diagnosis and screening of subpopulations of *Leishmania (Viannia) braziliensis*.

## **SUBPROJECT A**

A controlled, randomized, double-blind, and phase III clinical trial to verify the equivalence of effectiveness and compare the safety between standard and alternative dose regimens of meglumine antimoniate in the treatment of cutaneous leishmaniasis

### **A 5. Hypotheses to be tested**

#### **A 5.1 Non-inferiority of effectiveness**

$H_{0E}$  = There is no non-inferiority between the regimen currently recommended in Brazil for the treatment of cutaneous leishmaniasis (20 mg Sb5 + / kg / day for 20 days) and the alternative regimen with 5 mg for 30 days, i.e. the alternative scheme is not non-inferior to the standard regimen.

$H_{1E}$  = the alternative 5 mg schedule is non-inferior to the currently recommended 20 mg antimony regimen.

#### **A 5.2 Safety**

$H_{0S}$  = There is an equivalence of toxicity between the currently recommended regimen in Brazil for the treatment of cutaneous leishmaniasis (20mg Sb5 + / kg / day for 20) and the alternative regimen with 5mg for 30 days, i.e. no difference in toxicity between the schemes.

$H_{1S}$  = the currently recommended 20 mg regimen is more toxic than the alternative regimen.

Regardless of the therapeutic regimen, lesions located above the knees are expected to be epithelialized at the end of treatment, while epithelialization of localized lesions in the legs and feet occurs more frequently after the end of the treatment period. Administration of the drugs, particularly in those cases associated with vascular insufficiency. It is also expected that, regardless of the therapeutic regimen, patients over 50 years old present adverse effects more frequently and more intensely than younger patients.

## **A 6. Objectives**

### **A 6.1 General objective**

To compare the efficacy and safety of meglumine antimoniate at a dose of 20 mg Sb5+/kg/day for 20 days or at 5 mg for 30 days in the treatment of patients with cutaneous leishmaniasis.

### **A 6.2 Specific objectives**

1. To compare the immediate effectiveness (initial cure) and effectiveness after one year of follow-up (definitive cure) between the standard regimen recommended by the Brazilian Ministry of Health and the alternative regimen for the treatment of cutaneous leishmaniasis, with a non-inferiority margin of 15%.
2. To compare the frequency and severity of clinical, laboratory and electrocardiographic adverse effects among the different antimonial treatment groups.
3. Compare the frequency and severity of adverse effects and effectiveness among groups according to age, gender and race.
4. Compare the frequencies of epithelialization achieved on days 20, 30 and 50 of treatment among patient groups.
5. Compare the time in days until the epithelialization of the lesions according to the location above and below the knees, between the standard and alternative regimen of antimonial treatment, controlling for the concomitance with associated vascular insufficiency.

## **A 7. Subjects and methods**

### **A 7.1 Study outline**

Randomized, controlled to the standard treatment, double-blind and phase III clinical trial.

### **A 7.2 Description of the medication and schedule of interventions**

In Brazil, meglumine antimoniate (Aventis, São Paulo, Brazil) is stored at room temperature and distributed to the health network by the Health Surveillance Secretariat

- SVS / Brazilian Ministry of Health, which will provide a single lot to be used in all patients of the study.

This drug is for intramuscular (deltoid or gluteal) application in a single daily dose. Sterile plastic disposable syringes of 5 to 20 mL and disposable, sterile 25 × 7 mm needles will be employed.

The study using the intramuscular (IM) route without direct supervision will allow the evaluation of its use in real-world conditions (effectiveness) employed by the primary health services in the state of Rio de Janeiro. Although intravenous prescription is possible, it is not a usual route of antimony administration and it is also difficult to implement in an outpatient primary setting.

Each patient will be included in one of the following meglumine antimoniate treatment groups per IM route:

1. 20mg Sb5 + / kg / day for 20 days
2. 5mg Sb5 + / kg / day for 30 days

There will be no cross-over between the groups for the purposes of this study. The data of those patients who need a definitive interruption of a regimen will be analyzed according to the group to which they were randomized, which means, by intention to treat. Data collection will take place according to the consultation schedule.

### **A 7.3 Sampling plan**

#### **A 7.3.1 Sample size**

The groups with the minimum sample size (36 patients) are expected to respond to all the outcomes of interest.

We believe that the comparison of effectiveness between the two schemes will reveal non-inferior results to the alternative regimen for the following outcomes:

1. frequency of good initial response (evaluated on days 20, 30 and 50).
2. time (in days) until epithelization of all lesions is reached.
3. time (in days) to achieve total healing of all lesions.
4. frequency of good late response (one year of outpatient follow-up according to study schedule).

6. frequency of reactivation after treatment (up to two years of outpatient follow-up according to study schedule).

The significance level of 5% and power of 80% were used to calculate the required sample size to compare the frequencies of the outcomes of interest in the standard group with the other group. To test the non-inferiority between proportions in the primary endpoints of effectiveness, an acceptable limit of 15% difference between these healing ratios was considered. This will require 36 patients in each therapeutic regimen group.

Predicting the use of the McNemar paired test to compare the rates of healing or epithelialization on days 20, 30 and 50 will require at least 36 patients in each group (assuming a medically irrelevant difference of 30%).

To compare the effectiveness of treatment according to the location of the lesions, above or below the knee, only 12 patients will be needed in each treatment group.

It is expected that the alternative group (low dose, 5 mg Sb5+/kg/day) will present non-inferior results with a margin of 15%, and a lower frequency of clinical adverse effects, in addition to a low frequency of laboratory and electrocardiographic adverse effects. However, we expect to find a significant difference in the following outcomes when comparing the safety of the standard 20mg treatment with the alternative regimen:

1. frequency of clinical, laboratory or electrocardiographic adverse effects in any degree of intensity.
2. frequency of clinical, laboratorial or electrocardiographic effects of greater intensity.
3. frequency of treatment interruption caused by Adverse Events.
4. frequency of treatment dropouts.

In the case of elderly patients, a marked increase in the frequency and severity of AE in group 1 (20mg) is expected when compared to group 2 (5mg).

The significance level of 5% and the power of 80% were used to calculate the sample size needed to compare the standard group with the other group.

### **A 7.3.2 Allocation strategy (randomization)**

Eligible individuals (see eligibility criteria) who agree to participate (signing the informed consent form) will be allocated randomly in one of the treatment groups, according to the order of arrival, until the groups are completed. The randomized (numbered) allocation

list will be constructed in EPI-INFO 6.4 with the total number of subjects required for the survey and made available at the IPEC pharmacy. There will be stratification with interaction analysis of clinical and epidemiological aspects that may have a modifier effect on the endpoints (age, gender and race) and blocking with pre-defined blocks of twelve in order to ensure the balance between treatment groups at any time in case of need to stop the research.

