## **A 7.5 Study patients and schedule for inclusion**

The study will include 72 patients with CL coming from the State of Rio de Janeiro, attended at the Reference Center on Leishmaniasis - IPEC - Fiocruz.

As lesions located below the knee are expected to only be fully epithelized several weeks after the end of treatment, bias may occur in the assessment of treatment effectiveness if patients with this lesion location were more frequently present in a given treatment group. Likewise, patients older than 50 years usually present adverse effects more frequently and with greater intensity, and may negatively influence the safety assessment if they were present more frequently in a given group. These inclusion biases will be avoided through the strategy of block randomization and controlled with multivariate analysis, considering the following variables as potential confounders: age above and below 50 years and presence of lesions above and below the knees.

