### **A 7.11 Masking**

It was decided that a physician who was not aware of the therapeutic scheme would perform measurements of clinical (interest) and adverse (clinical) outcomes, in order to preserve masking between intervention and outcome. This step was taken to minimize the risk of ascertainment biases originated from differentiated outcomes according to the treatment scheme to which each patient belongs. The results of laboratory tests will be provided by the clinical pathology laboratory without information on the treatment group. Similarly, for analysis purposes, groups will not be identified. The database manager will preserve the confidentiality of this information by encoding the groups for analysis by the epidemiologist(s).

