## **A 7.16 Control of dispensing and storage of medications**

All ampoules needed for the complete treatment of the entire study population will be stored at the IPEC pharmacy. A trained team professional will recruit the patients at the day 1 appointment, following the randomization list from the trial previously provided by the Epidemiology sector. A trained pharmacist will dispense the medication prescribed by the Infectious Diseases expert physician by submitting the test card and the prescription.

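### A single disclosed block size of twelve, at one centre with visible regimens, lets staff who track the sequence foresee up to one assignment in seven; undisclosed varying sizes would be a cheap improvement

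*Protocol*

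**What the plan says.** - **Blocking.** A 7.3.2 specifies "blocking with pre-defined blocks of twelve in order to ensure the balance between treatment groups at any time in case of need to stop the" trial, and consenting patients are "allocated randomly in one of the treatment groups, according to the order of arrival". It describes one numbered list for the whole sample, available at the pharmacy. The same sentence names stratification by age, gender and race alongside an interaction analysis. It does not say whether the list itself is stratified, and it gives no cut-offs.
- **Size and setting.** A 7.3.1: "This will require 36 patients in each therapeutic regimen group". A 7.5: "The study will include 72 patients with CL coming from the State of Rio de Janeiro, attended at the Reference Center on Leishmaniasis".
- **Regimens.** A 7.2 sets two intramuscular regimens that differ fourfold in daily dose per kilogram and last 20 and 30 days. No dummy injections are described.
- **Who sees the regimen.** A 7.16: "A trained pharmacist will dispense the medication prescribed by the Infectious Diseases expert physician by submitting the test card and the prescription". The same section has the staff member who recruits on day 1 work from the randomization list.
- **Who is masked.** A 7.1 labels the trial double-blind. A 7.11 gives the detail: "It was decided that a physician who was not aware of the therapeutic scheme would perform measurements of clinical (interest) and adverse (clinical) outcomes". Laboratory results are issued without the group, and groups are coded for the analysis.
- **What the blocking must achieve.** A 7.5 relies on it to avoid inclusion bias from lesion site and from age over 50, with multivariate analysis as a second safeguard.
- **Sealed codes.** A 7.14 allows the codes to be opened only in an emergency. A copy is held by an epidemiologist outside the patient-care and analysis teams.

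**The concern.** In a 1:1 block of known size twelve, once one regimen has been given six times, every remaining place in that block goes to the other regimen. At one centre, with openly prescribed regimens of different dose and length, the information needed to work this out passes through the hands of the prescriber and the pharmacist. Keeping the list in the pharmacy does not remove that route, because it runs through past assignments and not through the list.

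Someone who foresees the next assignment can hurry or defer a patient. A 7.5 itself says which patients heal later and which have more adverse effects, so both the non-inferiority comparison and the toxicity comparison could be affected. The protection that A 7.5 expects from block randomization is weaker to the extent that assignments can be foreseen.

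**Working it through.** The protocol gives no figure for predictability, so there is none to reproduce.

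**Inputs from the protocol:** block size 12 (A 7.3.2); 36 per arm, hence 6:6 within a block (A 7.3.1); 72 patients at one centre (A 7.5); 15-point margin (A 7.17).

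**1. Certain assignments on one unstratified list.** After j assignments in a block, the next is certain if one arm has used all six places. The probability is 2·C(j,6)/C(12,6), with C(12,6) = 924.

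| Place in block | 7 | 8 | 9 | 10 | 11 | 12 |
|---|---|---|---|---|---|---|
| Probability certain | 2/924 | 14/924 | 56/924 | 168/924 | 420/924 | 924/924 |

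The sum is 1584/924 = 12/7 = 1.714 per block, so the share is 1/7 = 14.3%. With 72/12 = 6 blocks, this is 6 × 1.714 = 10.3 of 72 assignments.

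**2. Best guess.** Always guessing the arm that is behind in the block gives 6 + (4096/924 − 1)/2 = 7.716 correct of 12, or 64.3%, against 50% by chance.

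**3. If the strata are separate lists.** The number of cells is an assumption.
- Eight cells of exactly nine patients: only places 7 to 9 count, (2 + 14 + 56)/924 = 0.078 per cell, and 0.078/9 = 0.9%.
- Four cells of 18: one complete block each, 1.714/18 = 9.5%.
- Patients spread at random over equal cells: about 10.3% (four cells) and 4.9% (eight cells).
- Eight uneven cells: about 6% to 7.5%.

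The range is about 1% to 10%. One in seven is therefore the upper end. It applies where all blocks are completed.

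**4. Worst-case bias.** Assume that half of patients are favourable and that every certain slot is exploited: always a favourable patient for one arm, always an unfavourable one for the other. The favourable share is then 0.5 + 0.143/2 in one arm and 0.5 − 0.143/2 in the other, a difference of 14.3 points. The protocol gives no prognostic gap in cure, so a range is shown.

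| Assumed gap | Bias = gap × 0.143 | Share of the 15-point margin |
|---|---|---|
| 10 points | 1.4 points | 10% |
| 20 points | 2.9 points | 19% |
| 30 points | 4.3 points | 29% |

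Steering half of these slots successfully gives half of each figure.

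**5. Effect of varying the sizes.** Take blocks of 8, 10, 12, 12, 14 and 16 in random order (total 72, ending 36:36).
- Simulation with a guesser who knows this set of sizes and every past assignment: about 3% of assignments are certain.
- Best guess, by the formula in step 2: 5.33 + 6.53 + 7.72 + 7.72 + 8.89 + 10.05 = 46.2 of 72, or 64.2%.
- Small varying blocks (4, 6, 8) also give few certain assignments, about 2%, but raise the best-guess rate to about 68%.

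**The case against.** **The change does not touch general predictability.** This stands. Guessing the arm that is behind needs no knowledge of block sizes. Exploiting every guess at an assumed 30-point gap would give 30 × (2 × 0.643 − 1) = 8.6 points now and 30 × (2 × 0.642 − 1) = 8.5 points afterwards. Only the certain assignments fall.

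**One in seven is not established.** This stands in part. A reader might infer that one in seven assignments is certain under this plan. A 7.3.2 names stratification in the same sentence as the blocking, and separate lists lower the share. The single-list reading does have support: one numbered list, entry by order of arrival, and 72 = 6 × 12. The text does not settle it.

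**Nothing shows that staff track assignments.** A reader might also infer that the recruiting team sees every past assignment, or that patients will be steered. The protocol says neither. A 7.16 shows that the prescriber and pharmacist see the regimen, but not that they decide who enters or when. A 7.14 keeps the codes closed. Tracking is feasible at one centre, and that is as far as the text goes. Allocation after consent and in order of arrival also limits deferral once a patient has agreed.

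**Age and lesion site are already adjusted for.** Correct: A 7.5 names age over 50 and lesion site as covariates. What remains exposed is whatever else a clinician may notice and the model does not contain.

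**Twelve is already a long block.** Also correct. A fixed six would make 25% certain and a fixed four 33%. The weakness is that the size is fixed and disclosed, not that it is twelve.

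**List access is the more direct problem.** This stands. If the recruiter works from the list, as A 7.16 says, concealment may already be lost for every assignment. Block size matters once that is repaired.

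**Conclusion.** The point holds as a cheap improvement, secondary to the recruiter's access to the list in A 7.16. The protocol fixes and discloses one block size in a single-centre trial where the regimen is visible to the prescriber and pharmacist and masking covers only outcome assessment, laboratory and analysis. For someone who knows the size and tracks every assignment, up to 14.3% of assignments are certain beforehand if there is one unstratified list, and about 1% to 10% with four or eight separately listed strata.

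The worst-case bias of 1.4 to 4.3 points rests on an assumed prognostic gap, an assumed half of patients being favourable, and full exploitation of every certain slot. It shows scale and does not predict what will happen. The documents do not support a claim that allocation will be subverted, or that varying the block size would make it unpredictable.

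**What to change.** In A 7.3.2, replace "blocking with pre-defined blocks of twelve" with: *permuted blocks of randomly varying size; the sizes are held only by the Epidemiology sector and the pharmacy and are not disclosed to recruiting or prescribing staff.* One list that fits has blocks of 8, 10, 12, 12, 14 and 16 in random order. The sizes themselves belong in a restricted document, not in the protocol. Small blocks such as 4, 6 and 8 are not a good substitute, given their higher best-guess rate.

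Change A 7.16 at the same time so that the person who recruits does not work from the list and learns the assignment only after the patient is irrevocably entered. Without this, varying the block size achieves little.

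The cost is one regenerated list and a sentence in each section, with no extra patients or procedures. The certain share falls from 14.3% to about 3%, and lower if the set of sizes is not known. The downside bears on the stated purpose of balance on early stopping: the largest possible imbalance within a block becomes 8 instead of 6.

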## **A 7.4 Eligibility criteria**

### **A 7.4.1 Inclusion criteria**

1. cutaneous leishmaniasis (CL) with parasitological diagnosis by one or more of the following methods: direct examination (scraping or imprint), histopathology, culture, immunohistochemistry or PCR.
2. history of exposure in the endemic area of the state of Rio de Janeiro.
3. absence of previous treatment with meglumine antimoniate.

### **A 7.4.2 Exclusion Criteria**

1. women who do not use contraceptive methods or do so improperly.
2. pregnant women.
3. children under 13.
4. previous treatment with meglumine antimoniate.
5. use of immunosuppressive therapy (corticosteroid, chemotherapy for cancer) or use of medications for tuberculosis or leprosy.
6. presence of clinical baseline changes equivalent to adverse effect level> G3.
7. presence of laboratory abnormalities equivalent to adverse effect level> G2.
8. presence of baseline electrocardiographic changes equivalent to adverse effect> G4 and / or baseline QTc > 0.46ms (equivalent to G1 level A).

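### Exclusion 1 covers every woman not using contraception, so applied as written it removes postmenopausal and otherwise infertile women whom the age and gender comparisons need

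*Protocol*

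**What the plan says.** Exclusion 1 in A 7.4.2 removes "women who do not use contraceptive methods or do so improperly". The next two items remove "pregnant women" and "children under 13". The age limit is a lower one only, and the inclusion criteria in A 7.4.1 restrict neither age nor sex.

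Elsewhere the protocol shows interest in age and gender:

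- Objective 3 in A 6.2: "Compare the frequency and severity of adverse effects and effectiveness among groups according to age, gender and race".
- Allocation (A 7.3.2) plans "stratification with interaction analysis of clinical and epidemiological aspects that may have a modifier effect on the endpoints (age, gender and race").
- A 7.5 lists as potential confounders "age above and below 50 years and presence of lesions above and below the knees".
- A 7.3.1: "In the case of elderly patients, a marked increase in the frequency and severity of AE in group 1 (20mg) is expected".
- A 5.2, A 7.5 and A 9 all expect more frequent and more intense adverse effects in patients over 50.
- A 8.1 includes elderly patients with comorbidities among those who could benefit from lower doses.

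Pregnancy during the trial is a withdrawal criterion in A 7.13.

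**The concern.** The first exclusion sits next to the pregnancy exclusion and also catches improper use of contraception, so its purpose is evidently to avoid exposing a pregnancy to the drug. That purpose does not apply to a woman who cannot conceive. The criterion nevertheless turns on whether she uses contraception, not on whether she could become pregnant. A 60-year-old woman using none meets it.

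The group removed is one the protocol needs for its own questions. It asks about toxicity by age and by gender and expects the higher dose to be markedly worse in elderly patients. If the rule is followed, the older patients in the trial would be mostly or wholly men, and the safety results would say little or nothing about older women.

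**Working it through.** The protocol states no figure on this point, so there is none to reproduce. The check has three parts.

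**1. Is the criterion limited anywhere else?** The places that could supply a limit are the inclusion criteria (A 7.4.1), the other exclusions (A 7.4.2), the description of study patients (A 7.5) and the withdrawal criteria (A 7.13). None mentions childbearing potential, menopause or infertility. The criterion stands as worded.

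**2. What is lost if women over 50 are absent?** Take age (50 or under, over 50) by gender. Of the four cells, three remain: younger men, younger women using contraception, and older men.

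- Main effects: intercept, age and gender are 3 parameters on 3 cells, so they are estimable. The age effect comes from the men and the gender effect from the younger patients.
- Modification of the regimen effect: with two regimens there are 3 × 2 = 6 cells. Intercept, regimen, age, gender, regimen-by-age and regimen-by-gender are 6 parameters, so they are still estimable.
- Age-by-gender, and the regimen effect in older women in particular, need the missing cell and are not estimable. The main effects then rest on an absence of interaction that the data cannot check.
- The comparison of regimens within each remaining cell is still randomised.

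**3. How many patients could be affected?** Only the total of 72 (A 7.5) comes from the protocol. The two shares below are assumptions.

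Affected = 72 × (share who are women) × (share of those women who cannot conceive and use no contraception)

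| Women | 20% affected | 30% affected | 40% affected |
|---|---|---|---|
| 30% | 4.3 | 6.5 | 8.6 |
| 40% | 5.8 | 8.6 | 11.5 |
| 50% | 7.2 | 10.8 | 14.4 |

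The range is about 4 to 14, or 4.3/72 = 6% to 14.4/72 = 20% of the planned total. Split equally between two groups, it is about 2 to 7 women per regimen (4.3/2 to 14.4/2).

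**The case against.** The best defence is that the intent is plain. Any clinician would read the criterion as applying to women who could become pregnant, recruitment is by one team at one reference centre, and the loss arises only if that team applies the text literally. This is probably right about intent, but it does not remove the problem. The coordinators (A 7.15.1) and the external committee (A 7.15.2) are to check for protocol deviations, and a sensible enrolment would be a deviation from the written rule.

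Several stronger readings are tempting but are not supported:

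- A reader might infer that age and gender effects could no longer be separated, or that objective 3 could not be answered. The cell count above shows otherwise for the main effects. The protocol lists age, gender and race as separate factors and specifies no analysis of older women as such.
- A reader might infer that all sterile women are excluded. Surgical sterilisation may itself count as a contraceptive method. The clear cases are postmenopausal women and women infertile for other reasons.
- A reader might take A 8.1 to name the elderly as the principal beneficiaries. It includes them among a wider group.
- A reader might infer that the trial loses sample size. Enrolment runs to 72 regardless, and the programme has a separate study (subproject G) for patients excluded from this one. The cost is in who is represented.
- A reader might take 4 to 14 as an estimate. It is a product of assumed shares.

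**Conclusion.** The point holds as a matter of wording. Exclusion 1 is broader than its evident purpose and conflicts with the open upper age range, the age and gender comparisons, and the interest in patients over 50 and the elderly. Applied literally, it leaves few or no older women. The trial then loses the age-by-gender interaction and any safety conclusion for that group. Applied by intent, it produces avoidable breaches of a written criterion.

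The consequences stop there. Age and gender main effects remain estimable, and the primary non-inferiority comparison is valid in the patients enrolled. The near-absence of older women assumes literal application and that most women over 50 use no contraception. No count can be derived from the protocol. This is a free improvement and not a threat to the main result.

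**What to change.** Reword exclusion 1 so that it applies to women of childbearing potential who use no contraception or use it improperly, and leave exclusion 2 unchanged. The investigators should define childbearing potential on the screening form so that staff apply it uniformly. This reconciles the criterion with its purpose and with objective 3.

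The cost is a few words in the eligibility list and the form, with no added procedures or patients. No protection is given up, because the women readmitted cannot conceive and pregnancy remains both an exclusion and a withdrawal criterion. The change lets older women in but does not give power for an analysis of them: at the illustrative 2 to 7 per regimen, results for this group would be descriptive.

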#### **A 7.12 Criteria for definitive discontinuation of study treatment**

1. interruption caused by clinical, laboratory or electrocardiographic AE Grade 4
2. interruption longer than 10 days due to clinical, laboratory or electrocardiographic adverse effects Grade <3
3. spontaneous interruption of the use of prescribed medication in an amount greater than five consecutive doses due to failure of administration (non-adherence)

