#### **A 7.13 Criteria for withdrawal from the study (but not excluded from data analysis)**

1. definitive discontinuation of the treatment regimen for which it was randomized for any reason;
2. pregnancy;
3. need for introduction of immunosuppressive or potentially toxic drug (chemotherapy for cancer, tuberculosis or leprosy scheme);
4. Intercurrent disease, unrelated to the drug studied, but with manifestations equivalent or superior to clinical AD Grade 3;
5. need for re-treatment due to poor initial or late therapeutic response;
6. withdrawal of the patient from continuing in the study.

All patients will receive medical care at the leishmaniasis outpatient clinic of IPEC during the occurrence of adverse events. If necessary, the medication will be suspended for a maximum of 10 days and all affected patients will receive symptomatic treatment until the complete relief of the events temporally associated with the medication. They may have their treatment continued in an alternative regimen (but for the purposes of this clinical trial they will be analyzed by intention to treat, i.e. according to the group for which they were randomized). Whenever treatment is interrupted for safety reasons for more than 10 days, the patient will be withdrawn from the trial and restarted by intralesional treatment (subproject G).

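### The baseline ECG exclusion (A 7.4.2, criterion 8) cannot be applied as written: its QTc unit is wrong, its connector is undefined, and its grade limit does not fit the stopping rule

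*Protocol*

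**What the plan says.** Three sections of the protocol bear on this.

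- **A 7.4.2 Exclusion Criteria.** Criterion 8 reads "presence of baseline electrocardiographic changes equivalent to adverse effect> G4 and / or baseline QTc > 0.46ms (equivalent to G1 level A" (closing bracket follows). It has a grade limb and a QTc limb, joined by and/or. The neighbouring criteria use the same form: criterion 6 excludes "presence of clinical baseline changes equivalent to adverse effect level> G3" and criterion 7 excludes "presence of laboratory abnormalities equivalent to adverse effect level> G2".
- **A 7.12 Criteria for definitive discontinuation.** Item 1 is "interruption caused by clinical, laboratory or electrocardiographic AE Grade 4". Item 2 is "interruption longer than 10 days due to clinical, laboratory or electrocardiographic adverse effects Grade <3".
- **A 7.13 Criteria for withdrawal.** The closing paragraph says: "Whenever treatment is interrupted for safety reasons for more than 10 days, the patient will be withdrawn from the trial". It sets no grade condition.

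A 7.6.2 refers severity grading to annexes 1 and 2, which are not in the text at hand. It also defines an adverse event by its onset: while on the drug, or within 30 days of stopping it.

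**The concern.** Criterion 8 is the electrocardiographic entry check in a trial of a drug whose ECG effects are a stated safety outcome (A 6.2, objective 2; A 7.3.1). Whoever screens a patient must be able to apply the line in one way only. As printed, the screener has to guess the QTc unit, choose between 'and' and 'or', and decide whether a Grade 4 ECG change is acceptable at entry. Depending on those guesses the same line excludes everyone, some patients or possibly no one, so eligibility can be neither applied nor audited consistently. The admission limit also sits oddly beside the rule that ends treatment for an ECG event of Grade 4.

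**Working it through.** No sample size, power or alpha is involved. The check is a unit conversion followed by working through the possible readings.

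**Inputs.** From A 7.4.2(8): a QTc limit of 0.46 ms, glossed as Grade 1 level A; a grade limit strictly above 4; connector and/or. From A 7.12: Grade 4 in item 1, and below Grade 3 with more than 10 days in item 2. Assumed, because the annexes are not shown: a top grade of 4, with 5 as the alternative. No grade above 4 appears in the body of the protocol. QTc values from 300 to 550 ms are used as illustrations.

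**Unit.** 0.46 ms = 0.00046 s. Read in seconds, 0.46 s = 460 ms, and 460 / 0.46 = 1,000. Every value from 300 to 550 ms exceeds 0.46 ms. Against 460 ms the limb discriminates: 460 ms is not excluded and 461 ms is. The seconds reading is used here only to test the logic.

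**Gloss.** If everyone exceeds 0.46 ms, everyone would be at least Grade 1 on QTc. The line therefore contradicts itself, without any need of the annex.

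**Grade limb alone.** Strictly above 4 selects no grade on a scale ending at 4, and only Grade 5 on a scale ending at 5.

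**Combined, signs as printed, top grade 4:**

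| Unit | Connector | No ECG change, QTc 400 ms | Grade 4, QTc 400 ms | Grade 4, QTc 500 ms | Grade 1, QTc 470 ms |
|---|---|---|---|---|---|
| ms | or | excluded | excluded | excluded | excluded |
| ms | and | admitted | admitted | admitted | admitted |
| s | or | admitted | admitted | excluded | excluded |
| s | and | admitted | admitted | admitted | admitted |

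A Grade 4 baseline change is thus admitted under either 'and' reading. Under seconds with 'or' it is admitted only when QTc does not exceed the limit. Under the literal 'or' reading it is not admitted, because nobody is.

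**Entry against stopping.** With the signs as printed on a four-grade scale, criterion 6 admits clinical changes up to Grade 3, criterion 7 laboratory changes up to Grade 2, and the grade limb of criterion 8 ECG changes up to Grade 4. Only the ECG limit reaches the grade named in A 7.12(1).

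**Coverage in A 7.12.** Item 1 covers Grade 4. Item 2 covers grades below 3, that is 1 and 2. Grade 3 is in neither. A 7.13 covers any safety interruption of more than 10 days, Grade 3 included.

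**The case against.** The strongest reply is that this is a visible slip in one line. The Grade 1 gloss shows that the QTc limit was meant to discriminate, no one reading an ECG would apply 0.46 ms, and and/or is commonly taken as an inclusive 'or'. That is fair as to intent. It does not make the printed criterion correct, and a screening rule should not depend on the screener repairing it.

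The inequality signs may also have lost an inclusive bar. Criteria 6 to 8 share the same irregular form, and the sign in A 7.12(2) leaves out exactly the grade that an inclusive sign would cover. If so, Grade 3 is covered in A 7.12. A Grade 4 baseline change is then excluded in every combination except seconds with 'and', where it would still enter if QTc were within the limit. The text cannot settle this. The unit error and the open connector remain either way.

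Three stronger readings are tempting but not supported.

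- A reader might infer that the criterion both excludes everyone and lets Grade 4 ECGs in. These belong to different readings and cannot hold together.
- A reader might infer that a patient enrolled with a Grade 4 ECG already meets A 7.12(1), or that such patients would fill the safety and interruption counts. A 7.6.2 defines an adverse event by onset on or after treatment, so a stable baseline change is not literally a trigger and is not an adverse event.
- A reader might infer that a long Grade 3 interruption has no stated consequence. A 7.13 supplies one, whatever the grade.

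**Conclusion.** Criterion 8 is wrong as written. That the QTc limit is out by a factor of about 1,000 and contradicts its own Grade 1 gloss rests only on the printed line and on a human QTc being hundreds of milliseconds. The undefined connector is equally plain: with the limit in milliseconds and a top grade of 4, 'or' excludes 100% of patients and 'and' excludes 0%.

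The possible entry of a patient with a Grade 4 baseline ECG change is conditional. It needs the 'and' reading, or the seconds reading with QTc within the limit. It also rests on the annex scale and on the sign being as printed. It is a mismatch between entry and stopping rules, not a direct contradiction. The Grade 3 gap in A 7.12 is a secondary wording mismatch with A 7.13.

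No effect on sample size or the primary analysis was found. The reason to act is patient safety and consistent eligibility.

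**What to change.** 1. In A 7.4.2(8), state the QTc limit in its intended unit and confirm that it agrees with the Grade 1 gloss and the annex.
2. Replace and/or with a single connector.
3. Check the inequality signs in A 7.4.2(6) to (8) and A 7.12(2) against the original-language protocol and annexes 1 and 2.
4. Reconcile A 7.4.2(8) with A 7.12(1), so that the relation between the entry limit and the stopping grade is deliberate and stated. Reconcile A 7.12(2) with A 7.13, so that every grade, including Grade 3, is handled in the same way in both.

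The clinical limits are for the investigators to decide, and none is proposed here. The cost is about one corrected line in A 7.4.2 and one in A 7.12, plus the check against the annexes.
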